**Design Plan**

Study type

*Experiment - Randomized controlled trial.*

Blinding

*Personnel who analyze the data collected from the study will not be aware of the treatment applied to any given group.*

Is there any additional blinding in this study?

*The researchers will be divided into three teams; each team will have no contact with the others once recruitment begins until data analysis is complete. The participant recruitment will be conducted by Team 1. Team 2 will coordinate with external volunteers and ensure that the interventions are administered smoothly; they will also collect the data. Team 3 will analyze the collected data; they will have no contact with the participants.*

Study design

*This study will use a between-subjects design with four levels (Control, Yoga, Gita, Yoga+Gita), incorporating repeated measures of psychological distress at three time points to assess both immediate and long-term effects of the interventions. Randomization will ensure equal distribution across groups, and no counterbalancing is expected to be needed.*

Randomization

*The study will use simple randomization via a chit-pull system at the individual participant level, ensuring equal and unbiased assignment to one of the four study groups. There will be no additional stratifications or blocks. The chits will be placed in a glass bowl, folded, with no visible marks to enable identification of their contents. Each participant will remove one chit from the bowl, and the chit will contain the participant IDs and the group assignments.*

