Subgroup Analysis (by Gender, Educational Attainment, and Continued Practice): For the gender, education, and continued practice subgroup analyses, we will use the Mann-Whitney U Test to compare GAD7 scores between subgroups at each time point.

Effect Size Calculations: We will compute the Kendall’s W for effect size in the Friedman test and η² for the Kruskal-Wallis test to estimate the effect sizes. Statistical Significance: For all tests, a two-tailed p-value < 0.05 will be considered statistically significant.

Transformations

*None*

Data exclusion

*Participants who miss any follow-up session (B-GAD7, IPI-GAD7, DPI-GAD7) will be excluded.*

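### The team that coordinates the interventions also collects the GAD7, so the outcome collectors can be expected to know each participant's group; unattended completion by PIN would avoid this cheaply

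*Protocol*

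**What the plan says.** The Design Plan makes one blinding claim: "Personnel who analyze the data collected from the study will not be aware of the treatment applied to any given group". Under the question on additional blinding it divides the researchers into three teams, and "each team will have no contact with the others once recruitment begins until data analysis is complete". The duties are:

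- Team 1: "The participant recruitment will be conducted by Team 1".
- Team 2: it works with external volunteers and is to "ensure that the interventions are administered smoothly; they will also collect the data".
- Team 3: "Team 3 will analyze the collected data; they will have no contact with the participants".

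Under Randomization, each participant draws a chit, and "the chit will contain the participant IDs and the group assignments".

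The Sampling Plan adds a confidentiality safeguard. Scores are recorded by PIN only (Data Collection Process), and neither Team 2 nor Team 3 may see the list that links names to PINs (Data Management). Control receives nothing, while the other arms attend an hour a day for a week (Intervention Details). The GAD7 is the only outcome named (Variables). The protocol does not say whether it is self-completed or read out by staff.

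**The concern.** The team structure is offered as additional blinding, but it shields only the analysis. The GAD7 is a subjective scale, and answers on such a scale can be affected by who is present and what that person is connected with. Here the person who collects the form belongs to the team that arranged the sessions for three of the four arms. Participants in those arms have had a week of activity organised by that team; Control participants have had none.

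The comparison most exposed is that of the intervention groups with control after the intervention (study question 2). If contact with the collector leads active-arm participants to report less anxiety, the result looks like benefit. Blinding Team 3 cannot remove a shift that is already in the recorded scores.

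**Working it through.** **1. Can the collectors be expected to know group?** No part of the protocol says that they are masked. Team 2 cannot see that Yoga, Gita and Yoga+Gita sessions run daily for a week without knowing who belongs to which session, and whoever attends none is in Control. Team 2 then collects the immediate post-intervention score one day after the last session and the delayed score at 45 days. Baseline may be affected too. The draw follows consent, recruitment ends on 5 November and baseline is on 12 November; if chits are drawn before baseline, as that order suggests, group is already known then.

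**2. Does the PIN safeguard change this?** It keeps names off the data and withholds the name–PIN list from Team 2. It does not mask group, for two reasons: Team 2 meets intervention participants by group, and the chit carries PIN and group together.

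**3. How large could the effect be?** The protocol gives no estimate, and there is no figure of its own to reproduce: the sample-size inputs are stated but not the resulting number. What follows is an illustration under assumed shifts.

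Inputs from the protocol: difference 4 points, SD 3.78, two-sided 5%, 80% power, four equal arms, one-way ANOVA followed by Tukey's HSD if significant.

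Assumed: 16 completers per arm. The exact two-sample t-test needs n = 15.04 per arm for 4/3.78 = 1.058 SD, rounded up to 16. Also assumed: no true effect, normal scores, and all three active arms shifted down by the same b points.

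*Unadjusted two-sample t-test.* The standard error is 3.78 × √(2/16) = 1.336, the noncentrality is b/1.336, and the critical value on 30 df is 2.042.

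*Planned procedure.* The overall F must exceed 2.758 (3 and 60 df), and a pair must then differ by more than q × s/√16 with q = 3.737. At s = 3.78 that is 3.737 × 0.945 = 3.53 points. Rates are from 400,000 simulated trials per row.

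| Assumed shift b | Noncentrality | Unadjusted t-test | ANOVA + Tukey: one given active v control | ANOVA + Tukey: any of the three |
|---|---|---|---|---|
| 0 | 0 | 5.0% | 0.9% | 2.4% |
| 0.5 | 0.37 | 6.5% | 1.4% | 3.5% |
| 1 | 0.75 | 11.2% | 3.1% | 7.3% |
| 1.5 | 1.12 | 19.2% | 6.7% | 14.5% |
| 2 | 1.50 | 30.5% | 12.8% | 25.5% |

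The columns under the planned procedure are the relevant ones. A shift of 1 point, a quarter of the 4-point difference the trial is sized for, roughly triples the false-positive rate of any active-versus-control comparison (7.3/2.4 = 3.0).

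**The case against.** Several points on the other side are sound.

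- **The protocol never promises blinded collection.** It claims blinding of the analysts only. This stands: nothing in the document contradicts itself here.
- **Team 2 is not said to deliver the sessions.** A reader might infer that participants hand their scores to the people who taught them. The text has Team 2 coordinate with external volunteers, which points the other way. The inference that holds is narrower: the collectors know group and are connected with the sessions.
- **Collection is not fully unblinded.** That label would ignore the PIN procedure, which bears on candour because answers are not tied to names on the record. This stands as a partial safeguard, but it does not mask group.
- **Differential pursuit of missing forms is supposition.** The exclusion rule, "Participants who miss any follow-up session (B-GAD7, IPI-GAD7, DPI-GAD7) will be excluded", might suggest that an arm-aware team could influence who stays in the analysis. But the protocol describes no reminders and fixes one date per assessment for all arms.
- **Participants know their own arm.** If the GAD7 is self-completed, the participant is the assessor, and no change of collector can blind the outcome. This stands and limits what the fix can achieve.
- **Team 1 is not shown to be a blind alternative.** It finishes recruiting before baseline and might seem free to collect. But the protocol does not say who supervises the draw or holds the name–PIN list, and Team 1 is the only team not barred from that list.

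What is left is that arm-aware staff collect the trial's only outcome, and that the procedure can be changed at little cost.

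**Conclusion.** The point holds as a cheap improvement. Team 2's double role means that the outcome collectors can be expected to know group, the PIN procedure does not prevent this, and only the analysts are blinded. That leaves avoidable room for collector influence in the comparisons of active arms with control.

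The size is unknown. The 1.4% to 12.8% for one comparison, and 3.5% to 25.5% for any of three, depend on assumed shifts of 0.5 to 2 points, an assumed 16 per arm and normal scores. They also credit the whole shift to the collector, although part of any reporting bias would come from participants knowing their arm. A reader might take the unadjusted t-test rates of 6.5% to 30.5% as the trial's false-positive rate; the documents do not support that, because the plan uses ANOVA with Tukey's HSD. The direction, towards apparent benefit, is plausible but not demonstrated.

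**What to change.** Rewrite the data-collection duty in the Design Plan and the Data Collection Process as follows:

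- Participants complete the GAD7 unattended at all three time points, identified by PIN only, on an online form or on a sealed form placed in a drop box.
- Team 2 is not present and does not handle the forms. They go to Team 3 with arms coded, and the PIN-to-code list is prepared by someone outside Teams 2 and 3. This respects the rule that Team 3 does not meet participants.
- The same reminders go to everyone in all four arms at the same times.
- The protocol states that participants remain unblinded, so the change reduces collector influence but not all reporting bias.
- Team 1 collects only if it is kept away from the chit pull, the allocation list and the name–PIN link.

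The cost is a change of procedure with no added staff. The small downside is that nobody checks forms for completeness at hand-in; an online form that requires every item would deal with most of that.

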**Sampling Plan**

Existing Data

*None*

Data collection procedures

*Population:* The participants will be healthcare workers (HCWs) employed at Sri Jagannath Heath Care and Research Centre, Dhanbad, Jharkhand, India. They are facing significant psychological stress during this COVID-19 pandemic, making them suitable candidates for the study aimed at assessing interventions for stress reduction.

*Recruitment:* Participants will be recruited by posting a call for participation on the internal email system and notice board of the hospital. This announcement will include all relevant information about the study, such as the nature of the interventions, expected commitment, and the informed consent form. No payments will be provided for participation.

*Inclusion and Exclusion Criteria:*

Inclusion Criteria: Participants will be aged 18 years or over and be currently employed HCWs at the hospital. They will also need to be available for the entire duration of the intervention (1 week) and follow-up (45 days post-intervention).

Exclusion Criteria: Participants with pre-existing diagnosed mental health conditions will be excluded to ensure that the study focuses on measuring the effect of the interventions on psychological distress caused by work-related stress during the pandemic, rather than on pre-existing disorders.

*Grouping:* After the eligible HCWs return the signed informed consent forms, they will be randomized into one of four groups (Control, Yoga, Gita, Yoga+Gita) using a chit-pull system, as previously described, in a 1:1:1:1 ratio.

*Study Timeline:* Recruitment will begin on October 25, 2021, and end on November 5, 2021. The baseline assessment (B-GAD7) will be administered on November 12, 2021. The interventions (Yoga, Gita, Yoga+Gita) will be conducted between November 13, 2021, and November 19, 2021. The immediate post-intervention GAD7 (IPI-GAD7) will be collected on November 20, 2021 (1 day post-intervention). The delayed post-intervention GAD7 (DPI-GAD7) will be administered on January 3, 2022 (45 days post-intervention).

*Intervention Details:* Participants in the intervention groups will attend daily 1-hour sessions for one week. The Yoga group will practice yoga for the entire hour. The Gita group will attend Bhagavad Gita lessons for one hour. The Yoga+Gita group will have 30 minutes of yoga followed by 30 minutes of Bhagavad Gita lessons. The Control group will not receive any intervention.

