*Data Collection Process:* Psychological distress will be measured using the Generalized Anxiety Disorder-7 (GAD7) scale at three time points; Baseline (B-GAD7) - Administered before the interventions starts, Immediate Post-Intervention (IPI-GAD7) - Administered 1 day after the last intervention session, and Delayed Post-Intervention (DPI-GAD7) - Administered 45 days after the intervention. All data will be collected anonymously using only the participant identification numbers (PINs) to maintain confidentiality.

*Data Management:* The consent forms and a document linking participants’ names to their PINs will be securely stored and not accessible to the data analysis team or to the intervention coordination and data collection team. The data will include GAD7 scores and demographic information (age, gender, education level).

Sample size

*The sample size will be calculated to detect significant effects with 80% power to detect a minimum clinically important difference of 4 for the GAD7 with a standard deviation of 3.78 at the standard alpha error of 0.05. A dropout rate of 15% will be considered. PASS 2020, v20.0.6 will be used to calculate the sample size.*

Stopping rule

*None*

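### As written, B-GAD7 is most naturally read as taken after participants know their arm: a pre-treatment score, but not a pre-allocation baseline.

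*Protocol*

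**What the plan says.** Four parts of the protocol bear on the order of events.

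- **Trigger for the draw** (Sampling Plan, Grouping): "After the eligible HCWs return the signed informed consent forms, they will be randomized into one of four groups". No baseline step is named between consent and the draw.
- **What the chit carries** (Design Plan, Randomization): "Each participant will remove one chit from the bowl, and the chit will contain the participant IDs and the group assignments".
- **Dates** (Sampling Plan, Study Timeline): the recruitment window is given as "Recruitment will begin on October 25, 2021, and end on November 5, 2021". Baseline comes a week after that window closes: "The baseline assessment (B-GAD7) will be administered on November 12, 2021". Sessions follow from the next day; they "will be conducted between November 13, 2021, and November 19, 2021".
- **How data are identified** (Sampling Plan, Data Collection Process and Data Management): "All data will be collected anonymously using only the participant identification numbers (PINs) to maintain confidentiality". The list linking names to PINs is "not accessible to the data analysis team or to the intervention coordination and data collection team".

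The Data Collection Process places the baseline before the interventions start, not before allocation. Under Blinding, only those who analyse the data are said to be unaware of treatment; nothing hides the arm from participants. The Data exclusion paragraph removes anyone who misses any of the three assessments, B-GAD7 included.

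**The concern.** A baseline earns its role by being measured before anyone can react to the allocation. GAD7 rates subjective distress, and one of the four arms receives nothing. A worker who already knows which arm they drew may answer differently out of relief, disappointment or anticipation. Such a shift could differ by arm, and its direction cannot be predicted from the documents.

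Two consequences follow. First, any analysis that compares a later score with B-GAD7 would mix the effect of the intervention with the reaction to the draw. Study question 1 (reduction from baseline) and question 5 (stability in Control) rest on exactly this comparison. Second, someone who knows their arm may choose not to turn up for B-GAD7. Because that leads to exclusion, randomized participants could be lost selectively by arm before the first session.

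**Working it through.** **1. Order of events.** No sentence dates the draw, so the order has to be pieced together.

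- B-GAD7 is filed by PIN only (Data Collection Process).
- The team that collects data cannot look up a PIN from a name (Data Management), so the participant must already hold it.
- The only described source of a participant number is the chit (Randomization), taking the participant ID and the PIN to be the same number.
- The chit also shows the arm.

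Hence B-GAD7 cannot be filed as described until the arm has been drawn. The draw's placement after consent, with no baseline step between, fits this.

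**2. Dates.**

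- Recruitment closes to B-GAD7: 5 to 12 November = 7 days.
- Recruitment opens to B-GAD7: 25 October to 12 November = 18 days.
- B-GAD7 to first session: 12 to 13 November = 1 day.

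If chits are drawn as consent is returned within the recruitment window (an assumption), participants know their arm 7 to 18 days before B-GAD7.

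**3. Which planned analyses use B-GAD7** (Study questions; Analysis Plan).

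| Analysis | Uses B-GAD7 values? |
|---|---|
| Within-arm repeated measures; baseline vs IPI and baseline vs DPI (questions 1, 5) | Yes |
| Question 4, if read as a reduction from baseline | Yes |
| Subgroup changes over time | Yes |
| One-way ANOVA across arms at baseline | Yes |
| One-way ANOVA across arms at IPI and at DPI (questions 2, 3, 6) | No |

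**4. Scale.** The protocol gives an MCID of 4 and an SD of 3.78. The size of any reaction is not given, so a range is assumed. A shift in B-GAD7 passes in full into the change score:

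- 0.5 point: 0.5/4 = 12.5% of the MCID; 0.5/3.78 = 0.13 SD
- 1 point: 1/4 = 25%; 1/3.78 = 0.26 SD
- 2 points: 2/4 = 50%; 2/3.78 = 0.53 SD

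The protocol states no sample size. For scale only, one two-sided pairwise comparison at 5% with 80% power needs n = 2(1.96 + 0.842)²(3.78/4)² = 14.02, rounded up to 15 per arm.

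With 15 per arm and an assumed within-person correlation ρ of 0.3 to 0.7, the SD of change is 3.78√(2(1−ρ)), which is 4.47 down to 2.93. The standard error of a mean change is that divided by √15, or 1.15 down to 0.76. A 1-point shift is therefore about 0.9 to 1.3 standard errors.

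A simulation on these inputs (20,000 runs, normal scores, no true effect) gave these rejection rates:

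| Assumed shift in B-GAD7 | Paired baseline-vs-later test at 0.05/3 (nominal 1.7%) | Between-arm test of change (nominal 5%) | Between-arm test of the later score alone (nominal 5%) |
|---|---|---|---|
| 0.5 | 2.5–3.6% | 6–8% | about 5% |
| 1 | 5.4–11.5% | 9–14% | about 5% |
| 2 | 20–49% | 22–43% | about 5% |

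The paired column leaves out the omnibus repeated-measures test that the protocol requires first. The change column bears only on a change-based reading of question 4; the planned across-group test is not a test of change.

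**5. Loss at baseline.** The last column shows that a shift in B-GAD7 values does not disturb the IPI and DPI comparisons. Arm-dependent absence from B-GAD7 could, because those absent drop out of every analysis. The documents give nothing from which to size this.

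**The case against.** The best reply is that the protocol never says B-GAD7 follows the draw. It says only that randomization comes after consent. A PIN could be issued by some other route, or the ID on the chit might not be the PIN. This stands to the extent that the order is an inference. It does not remove the point, because no other source of the PIN is described and nothing places B-GAD7 before the draw.

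A second reply is that B-GAD7 still precedes every session, which is all the protocol promises. This also stands. A reader might infer that the baseline is invalid altogether; the documents do not support that. What is missing is a baseline taken before allocation is known.

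A third reply is that the main between-arm comparisons are untouched. For B-GAD7 values this is right: the ANOVAs at IPI and DPI ignore them, and the protocol plans no baseline-adjusted model through which a shift could enter. A reader might infer that every treatment comparison is biased. The text supports only the narrower route through exclusion, and that rule covers missed IPI and DPI assessments as well, so it is not purely a baseline problem.

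Finally, the statement "The study will use simple randomization via a chit-pull system at the individual participant level, ensuring equal and unbiased assignment" might lead a reader to infer that arm sizes will be badly unequal, since simple randomization does not guarantee equality. Chits that carry individual IDs fit better with a finite bowl drawn without replacement, and a 1:1:1:1 ratio is stated. Independent draws are therefore not a fair model of this procedure. The label is a separate wording matter.

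**Conclusion.** The point holds in limited form. On the most natural reading, participants know their arm when B-GAD7 is taken, so it is a pre-treatment but not a pre-allocation baseline. This rests on treating the participant ID and the PIN as one number and on the chit being its only source.

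The analyses at risk are the within-arm tests against baseline (questions 1 and 5), any change-based reading of question 4, subgroup changes over time, and the baseline comparison of arms. A 1-point reaction, which is an assumption, would be 25% of the MCID of 4; the true size and direction are unknown. The IPI and DPI between-arm ANOVAs are affected only if absence from B-GAD7 depends on the arm.

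This is a cheap improvement to make before recruitment opens, not a defect that undermines the whole trial. Once participants know their arm, no analysis can recover a pre-allocation baseline.

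**What to change.** Issue the PIN on its own slip when consent is returned. Let participants draw or open the arm chit only after B-GAD7 has been handed in, and record the arm against the PIN at that moment. State the date of the draw, and state that B-GAD7 precedes disclosure of the arm. Anyone who misses B-GAD7 is then never allocated, which removes arm-dependent loss at that visit.

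There are two ways to time this, each with a cost:

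- **B-GAD7 on 12 November, draw straight afterwards.** Participants get about one day's notice of their sessions. The Design Plan gives recruitment to Team 1 and data collection to Team 2, with no contact between them once recruitment begins. A hand-off is needed, for example a receipt for B-GAD7 that the participant carries to the draw, and the no-contact rule should be worded to allow it.
- **B-GAD7 collected with the consent form.** Notice of sessions is no longer short, but baseline moves from 1 day to between 8 days (5 to 13 November) and 19 days (25 October to 13 November) before the first session. The task also has to be shared or reassigned between the teams.

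If the draw has already taken place, report its date relative to B-GAD7, describe B-GAD7 as pre-treatment but post-allocation, and report by arm how many drew a chit and did not complete B-GAD7.
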